## Pilot Study Results

To determine if the electronic retrieval of the community drug list would add value to the usual care process, we conducted a pilot study at the McGill University Health Center. To access medications from community pharmacies, we used an integrated drug management system (MOXXI) that our research group had already developed to provide on-line access to the Quebec government prescription database of all medications from community pharmacies. The MOXXI system provides near real-time information (within 24 hrs.) on dispensed prescriptions from the 1,800 community pharmacies in Quebec through a secure virtual private network that links to the prescription claims adjudication system of the government insurer (RAMQ). 135 primary care physicians and specialists and 92,500 patients use MOXXI as part of an on-going research program on the impact of information technologies on the quality of care. In the pilot study, we assessed whether the community drug profile identified missing medication at admission, the value for the treatment team, and the number of community providers who would be affected by a discharge reconciliation and communication intervention. In 91 consecutive patients admitted in 2009, we showed that electronically retrieved community pharmacy records identified, on average, 3 additional drugs per patient. For 21% of patients,  $\geq 5$  drugs were identified (Figure 1).

**Figure 1 Differences in the Community Drug Profile  
ER Medication History vs. Community Pharmacy Records**

[figure not shown]

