Third, the *discharge communication module* (Figure 6) will facilitate the identification and transfer of information on discontinued and changed medication to the respective dispensing pharmacy (ies) and prescribing physician(s) along with the reasons for these changes. The attending physician/resident will document *the reason for discontinuing or changing the dose of each medication* using a drop-down menu, an approach that has been validated by our group in prior research. A comment field is also available where additional information can be added using free text. The list of prescribed and discontinued medications will be printed, signed by the attending physician/resident, and a copy printed and retained for the chart.

Figure 6 Discharge Communication Module

For each discontinued medication or dose change, the dispensing pharmacy and prescribing physician will be identified from the community-based pharmacy claim record. The identity of the prescribing physician and pharmacy must be completed accurately for the pharmacy to receive payment from the RAMQ. Access to this information has been approved for this study by the provincial privacy commission (appendix 3). For each discontinued drug, the name of the patient, drug, and the reason for discontinuation, attending physician, hospital, and discharge date will be faxed to the respective dispensing pharmacy and prescribing physician. Fax numbers for prescribing

physicians will be retrieved from the Collège des médecins du Québec who will provide the research team with a monthly updated file of all licensed physicians in Quebec, their telephone and fax numbers. Fax numbers for community pharmacies will be retrieved from Vigilance, a pharmacy software provider that receives a monthly update of this information from the Association Québécoise des Pharmaciens Propriétaires, that is used by pharmacies to fax transferred prescriptions from one pharmacy to another. To

minimize the risk of transmitting confidential information to incorrect fax numbers, we will call the pharmacy and physician's office before faxing patient information to verify the fax number.

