**Bias Control** The main challenge in *bias control* is the inability to blind staff to treatment assignment, and potential co-intervention. To control bias, the research assistant, expert panel, and analyst assessing the outcome of treatment will be blinded to unit and treatment allocation status. To assess bias related to possible co-interventions, the project coordinator will conduct a monthly review with the unit directors and hospital pharmacy to assess co-interventions (new initiatives that may modify the study outcomes), and we will use sensitivity analysis to assess the potential impact on the study outcomes. As the involvement of the hospital pharmacist in the patient's care likely reduces the risk of adverse events (e.g. through medication review), we will retrieve this information from the chart and assess whether hospital pharmacist intervention (yes vs. no) is a confounder by including this information as a patient-level variable in the analysis. In addition, as cluster randomization may not produce patients groups who have an equivalent risk of adverse events post-discharge (i.e. because randomization is by unit rather than by patient), we will assess whether patients admitted to the usual care vs. e-discharge units had a similar rate of hospitalizations, and ER visits in the 12 months prior to admission using RAMQ medical service data retrieved for each patient, and include prior ER/hospitalization history in the analysis to determine if it confounds the estimated effect of the intervention.

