Most adverse events occur early in the post-discharge period, therefore, we will conduct the follow-up interview in the first 25 to 30 days post-discharge. A trained research assistant will conduct patient follow-up interviews, **blinded** to intervention status. Five attempts will be made to contact the patient. If a patient cannot be reached successfully, we will send a questionnaire version of the adverse reaction and event report by mail, with an accompanying letter from their attending physician, and self-addressed stamped envelope for return. We will assess the quality of the interview and documentation provided by the research assistant by a monthly quality control check using standardized patient interviews. These quality control methods, that have been employed by our team in past research, will allow us to estimate the agreement between actual documentation and expected documentation, where the standardized case represents the gold standard. Additional training will be employed as needed to correct deviations from the protocol. Patient interview data will be entered into an ACCESS database.

*Chart Abstraction:* For each patient, a trained nurse abstractor, blinded to intervention status, will abstract the medical chart. We will abstract dates of admission and discharge, admitting and discharge unit, patient demographics, health problems at admission and discharge, major procedures (surgeries, treatment interventions), and medications at admission, during the hospital stay and at discharge, including medications that were stopped and changed by the in-hospital treatment team. Health problems will be coded using ICD10, medications by generic chemical code using Anatomic-Therapeutic Classification system, and procedures by Canadian Classification and Diagnostic and Therapeutic Procedures (CCP). Data will be entered using the MOXXI chart abstraction system as it permits text entries (e.g. hydrochlorithiazide 10mg, rheumatoid arthritis) to be mapped to the respective classification system and stored by patient identifier in the MOXXI Oracle database. A case summary record, that includes the community drug list, hospital drug list, discharge abstract, discharge medications and patient self-report, will be prepared for causality assessment by the expert panel.

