### **Data Management and Analysis**

---

Four sources of data will be assembled and linked to address the study objective: 1) abstracted medical chart documentation of patient demographics, admission and discharge dates, the community drug list, discharge prescription, and admitting and discharge diagnoses, 2) adverse events information and assessment post-discharge, 3) the RAMQ medical services and prescription claims data, and 4) co-intervention data collected by the study co-ordinator. All data will be managed in an Oracle database, and files for individual patients will be linkable through a study identification number and Quebec medicare number, with nominal information retained in a separate encrypted file.

The integrity of randomization will be assessed by characterizing the age, sex, baseline number of visits, hospitalizations, medications, and co-morbidity (using the Charlson co-morbidity index, a weighted index of conditions that increase the risk of mortality) of patients randomized to discharge reconciliation and usual care. The CONSORT guidelines will be followed to document the eligibility and follow-up of patients and inpatient units (clusters) in the trial. The provincial health administrative data will be used to characterize bias related to patients lost to follow-up after discharge for whom adverse drug events cannot be measured, based on the secondary outcome (re-admission/ER visits) as this can be measured on all patients.

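### The chart abstractor cannot stay blinded, and the causality panel's drug information is built from a different source in each arm with no masking step described

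*Protocol*

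**What the plan says.** Three parts of the protocol bear on this.

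- **Blinding.** The Bias Control paragraph of the Interventions section promises that "the research assistant, expert panel, and analyst assessing the outcome of treatment will be blinded to unit and treatment allocation status". Outcome Assessment adds that "a trained nurse abstractor, blinded to intervention status, will abstract the medical chart".
- **What is in the chart.** In the intervention arm, the description of the discharge communication module states: "The list of prescribed and discontinued medications will be printed, signed by the attending physician/resident, and a copy printed and retained for the chart". The usual-care description mentions no such document; there the patient leaves with a written discharge prescription.
- **What is taken from the chart and passed on.** The Chart Abstraction text begins "We will abstract dates of admission and discharge, admitting and discharge unit" and goes on to cover drugs stopped and changed in hospital. The panel then receives "A case summary record, that includes the community drug list, hospital drug list, discharge abstract, discharge medications and patient self-report". Data Management and Analysis lists as its first data source "abstracted medical chart documentation of patient demographics, admission and discharge dates, the community drug list".

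The community list has a different origin in each arm. The intervention list is retrieved electronically from RAMQ claims, then verified with the patient and supplemented. The usual-care list is documented by nurses, physicians and sometimes a pharmacist.

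**The concern.** The primary outcome is a judgement. An event counts when the panel rates it as definitely or probably drug-related on the Naranjo criteria. A judged outcome in a trial with unblinded staff is credible only if the judges see the same kind of evidence in both arms and cannot tell which arm they are looking at.

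As written, the evidence is gathered by someone who can identify the arm, and one of its main components comes from a different source in each arm. The protocol claims blinding for all those who handle the outcome but gives no procedure that would deliver it. If causality ratings shift in one arm only, the intention-to-treat GEE analysis cannot separate that shift from a treatment effect.

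**Working it through.** The protocol states no figure on this point, so the main check is to set its statements side by side.

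**1. The abstractor.** To record discharge drugs and stopped or changed drugs, the abstractor must open the chart. In intervention units it holds the signed module list ("a copy printed and retained for the chart"). Seeing that document identifies the arm. The abstractor also records the unit. Because units are the randomised clusters, a few charts with and without the printout are enough to learn which units belong to which arm. The stated blinding cannot be kept.

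**2. The drug list.** The case summary includes the community drug list, and Data Management and Analysis names chart documentation as its source. That list begins as claims in one arm and as a staff-taken history in the other. Stopped and changed drugs are abstracted in both arms, but a community drug missing from the chart cannot be recorded as stopped. The completeness of that information therefore depends on the same list.

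The pilot shows that the two sources differ: "electronically retrieved community pharmacy records identified, on average, 3 additional drugs per patient" beyond the ER medication history.

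**3. The panel.** It is promised to be blind to unit and allocation. Outcome Assessment describes it as reviewing each patient's chart and interview, and gives each clinician all clinical information retrieved from the chart. No removal of unit, module output or reason fields is described.

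**4. Where a difference can act.** Symptoms are found by a blinded telephone interview, so detection does not depend on the chart. The exposed step is the causality classification, which defines the primary outcome.

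**5. Sensitivity, on assumed values only.** Let k be the relative change in the intervention arm's classified rate caused by information or awareness of arm. The documents give no value for k.

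- Design effect implied by the protocol's own sample sizes: (4,423 − 2,852)/(0.05 − 0.02) = 52,367; 2,852 − 0.02 × 52,367 = 1,805; 52,367/1,805 = 29 = m − 1. At a correlation of 0.03, 1 + 29 × 0.03 = 1.87.
- Effective n per arm: (3,376/2)/1.87 = 903.
- Chance of a significant result: Φ[(d − 1.96·SE0)/SE1], with SE0 = √(2p̄(1−p̄)/n) and SE1 = √([p1(1−p1) + p2(1−p2)]/n). A two-sided 5% test is assumed.
- Example, k = 1.1: recorded rates 15% and 11%, SE0 = 0.01583, SE1 = 0.01580, (0.04 − 0.03103)/0.01580 = 0.568, giving 71.5%.

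| k | Recorded, true 15% v 10% | Chance of showing benefit | True 15% v 15%: false benefit | True 15% v 15%: false harm |
|---|---|---|---|---|
| 0.8 | 15% v 8% | 99.7% | 46.2% | 0.0% |
| 0.9 | 15% v 9% | 97.6% | 14.7% | 0.2% |
| 1.0 | 15% v 10% | 89.5% | 2.5% | 2.5% |
| 1.1 | 15% v 11% | 71.5% | 0.2% | 13.9% |
| 1.2 | 15% v 12% | 46.2% | 0.0% | 40.4% |
| 1.3 | 15% v 13% | 23.1% | 0.0% | 71.6% |

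The 89.5% at k = 1 exceeds the planned 80% because these rates need only 2 × 686 × 1.87 = 2,566 patients, not 3,376. That is a separate matter. If cluster size is instead taken as 3,376/28 = 121, the design effect is 4.59 and the chances of showing benefit at k = 0.9, 1.0 and 1.1 are 70.8%, 53.6% and 36.4%. The table shows only how sensitive the comparison is; it does not estimate the bias.

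**The case against.** The strongest reply is that the panel never handles the raw chart. Abstracted data are coded to standard classifications and assembled into a case summary whose listed contents do not include the printout, the reason fields or the unit. The abstractor transcribes and does not adjudicate, and the promise of blinding to unit does not extend to the abstractor. Outcome Assessment also says that administrative data on drugs will be retrieved, and prescription claims are linked for the study.

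Much of this stands, and it rules out several stronger readings that a reader might infer:

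- **That the panel sees the printout, so its blinding fails.** The documents do not show this. They leave the masking step undescribed, and the wording about chart review and all clinical information keeps the question open.
- **That stops and changes are documented only in the intervention arm.** They are abstracted for every patient. The usual-care remark that instructions may or may not be given concerns the patient, not the chart.
- **That the arms' lists differ by 3 drugs per patient.** The pilot compared the ER history with claims. The usual-care list may later be updated by physicians, nurses and pharmacists, and the intervention list is verified with the patient, so the gap between final charts is not known.
- **That the bias runs against the intervention.** Fuller lists could raise attribution to drugs or reveal another explanation, and awareness of arm could favour the intervention.

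The reply does not settle the source of the list. Administrative data are mentioned, but nothing places them in the case summary, and the data-source list assigns the community drug list to the chart.

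**Conclusion.** The point holds in a limited form. It is firm that the abstractor cannot be blinded as stated. It also follows from the text that the community drug list in the case summary is chart-derived and originates differently by arm, so the information behind the causality rating can differ by arm. That the panel could learn the arm is a possibility left open by the absence of any described masking, not a demonstrated failure.

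The size and direction of any bias are unknown. The sensitivity figures rest on assumed k, the protocol's 15% and 10% rates and its implied design effect. They show that a relative shift of 10% to 20% in one arm would matter in either direction. The conclusion assumes that the case summary is prepared as described, without an unstated step that replaces the chart list with claims.

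**What to change.** Before the first case summary is prepared, amend Outcome Assessment and Data Management and Analysis as follows:

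- In both arms, build the case summary's community drug list from the RAMQ prescription claims already linked for the study. Coverage by the public drug plan is an eligibility criterion, so claims should be available for all participants. The rule already used for the intervention list (active supply in the 7 days before admission) could define the list in both arms.
- Show discharge drugs, and stop/change status derived by comparing the two lists, in one common template.
- Exclude the unit, the module printout and the reason fields from everything the panel receives.
- State that the abstractor is not blinded, and that blinding applies to the interviewer, panel and analyst.

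The cost is some programming of the template from data already held. There is one small loss: over-the-counter and herbal products added at patient verification are not in claims. They would have to be left out of the common list or taken from the patient interview, in the same way in both arms.

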## Study Population

**Eligibility:** The target population comprises patients who are at risk of preventable adverse drug events during transitions between community and hospital care. This population represents approximately 60% of the 3.1 million patients admitted to hospital each year in Canada, of whom 93,000 to 428,000 are expected to experience an adverse drug event. The study will be conducted at the McGill University Health Centre, a network of teaching hospitals that serve a population of 1.3 million Quebecers from Montreal to James Bay, including a trauma center, two tertiary adult hospitals, a psychiatric facility and a specialized hospital for respiratory disease. Teaching hospitals represent approximately 28% of hospital beds in

Canada, but they treat a higher proportion of complex, vulnerable patients where improvements in medication safety would have the greatest benefit. Patients will be eligible for inclusion in the study population if they are: 1) using prescription medication at admission, 2) covered by the Quebec drug insurance plan, 3) admitted from the community, 4)  $\geq 18$  years old at admission, 5) admitted to a general or intensive care medical, surgical or psychiatric unit, 6) discharged alive. Patients who are cognitively impaired or otherwise unable to provide consent will be included as we have shown that this subpopulation of patients may be at greatest risk of adverse events because of communication problems. Tri-council ethics guidelines deem that this subpopulation should not be excluded from interventions that potentially provide direct benefit to the participant because of the inability to provide informed consent (Article 4.5). For these patients, the family if present, or the medical director of the admitting unit will authorize study participation. Demographic, clinical and health care service use characteristics of the study population will be retrieved from the admission note, and provincial health care administrative databases in the year before admission and in the two months after discharge to characterize the study population, evaluate the integrity of randomization, assess potential biases related to losses to follow-up, and assess re-admission.

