*ER Visit/Hospital re-admission:* All visits to the emergency room and/or hospital re-admission in the 30 days post-discharge will be measured using the RAMQ provincial health care databases. This approach ensures that all ER visits and re-admissions are included, not just those occurring to at the MUHC. This is

important because ambulances will transport individuals to the closest, open emergency room/hospital which often is not the discharging institution. Almost all hospital-based physicians in Quebec are remunerated on a fee-for-service basis, and for each medical service delivered, physicians are required to accurately record the treating establishment, and the location of the service (e.g. ICU, ER, day hospital, inpatient unit), because location and type of establishment determine the level of remuneration. For each consenting patient, the RAMQ will retrieve all records of services provided in the month after discharge. Patients will be classified as having an ER visit if they have a record of service with a location of a hospital emergency room, and a re-admission if they have a service delivered from an in-patient general hospital unit. In secondary analysis, we will retrieve all ICD10 diagnostic codes recorded for ER visits and re-admissions to provide descriptive information on potential reasons for the visit/re-admission.

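### The claims rule for re-admission conflicts with the protocol's statement that all re-admissions are counted, and it does not require a new stay

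*Protocol*

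**What the plan says.** All of the outcome text is in the Protocol, Outcome Assessment, under ER Visit/Hospital re-admission.

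- Scope: "All visits to the emergency room and/or hospital re-admission in the 30 days post-discharge will be measured using the RAMQ provincial health care databases".
- Stated advantage of claims: "This approach ensures that all ER visits and re-admissions are included, not just those occurring to at the MUHC".
- ER rule: "Patients will be classified as having an ER visit if they have a record of service with a location of a hospital emergency room".
- Re-admission rule: "a re-admission if they have a service delivered from an in-patient general hospital unit".
- Retrieval period: "the RAMQ will retrieve all records of services provided in the month after discharge".
- Fields available: "physicians are required to accurately record the treating establishment, and the location of the service (e.g. ICU, ER, day hospital, inpatient unit".

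Diagnosis codes are also retrieved, but only to describe likely reasons for the visit or stay. They do not enter the classification.

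The Study Population section says that the network includes "a psychiatric facility and a specialized hospital for respiratory disease". It admits patients from both ordinary and intensive care units in medicine, surgery and psychiatry. Patients must have been "admitted from the community" and must leave hospital alive; no condition is set on where they go.

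**The concern.** The section makes a completeness claim and then gives a rule that is narrower than the claim in one respect and wider than re-admission in another. It is narrower because the undefined word general appears to remove some inpatient settings. It is wider because one billed inpatient service is enough, with no requirement that a new stay has begun.

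Both faults act on a named study objective. The same measure is used in three further places. Data Management and Analysis uses it to judge bias from patients whose adverse drug events could not be measured, and also tests whether the effect differs between medicine, surgery and psychiatry. The section on monitoring study outcomes has the board review re-admission and ER rates each quarter. A rule that two programmers could code differently affects all of these.

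**Working it through.** The protocol has no figure of its own to reproduce here, so the check is mainly a comparison of passages.

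**1. The rule against the completeness claim.** The claim covers all re-admissions anywhere. The rule covers inpatient services in a general hospital unit. The meaning of general decides what is lost.

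- *General as a type of hospital.* Claims record the treating establishment, and the section says that type of establishment affects payment, so this is a natural reading. A stay in a psychiatric or specialised hospital then fails the rule. The study network has one of each.
- *General as opposed to intensive care.* The eligibility text uses the word this way and applies it to medical, surgical and psychiatric units alike. Psychiatric ward stays then count, but services billed from intensive care do not. The outcome section itself lists ICU and inpatient unit as separate locations. This gap is smaller, because a patient who later moves to a ward within the window is still picked up by a ward service.

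Each reading leaves something out of a set described as complete.

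**2. The rule against the idea of a re-admission.** The test is one service in the period.

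- *Direct transfer.* A patient who leaves a study unit alive for a bed in another hospital satisfies eligibility, which sets no destination. The first inpatient service billed at the receiving hospital satisfies the rule. The patient has not yet left inpatient care.
- *Discharge day.* The protocol speaks of 30 days and of a month after discharge, and does not say whether the day of discharge is inside. If it is, an inpatient service from the index stay billed that day satisfies the rule.

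Nothing later removes such records, because diagnosis codes are descriptive only.

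**3. How far it reaches.** Study Design lists 16 medical, 10 surgical and 2 psychiatric units.

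- Psychiatric share of units: 2/28 = 7.1%.
- Medical and surgical share: 26/28 = 92.9%.

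The share of patients in each type is not given. Nor does the protocol say whether the 2 psychiatric units are in the psychiatric facility or in a general hospital.

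**4. Size.** The protocol gives no rate of transfer, of discharge-day billing, or of re-admission to psychiatric, specialised or intensive care units, so no size can be derived. Only the direction of the false-event problem can be shown, on assumed values. Let *r* be the relative risk for genuine re-admissions. Let *s* be the share of counted re-admissions in usual care that are false and that the intervention leaves unchanged. Then

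observed relative risk = *s* + (1 − *s*) × *r*.

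With *r* = 2/3 (assumed):

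- *s* = 0.10: 0.10 + 0.90 × 2/3 = 0.70
- *s* = 0.20: 0.20 + 0.80 × 2/3 = 0.73
- *s* = 0.30: 0.30 + 0.70 × 2/3 = 0.77

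This is movement towards no effect. It concerns re-admission alone, whereas the analysed outcome combines ER visits and re-admission, so the share of false events in that composite could be smaller.

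**The case against.** The strongest reply has four parts.

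- *Claims algorithms belong in an analysis plan.* Linking episodes and handling transfers are often left there, and that plan is not shown. This would settle the matter if the protocol were silent. It is not: it states an operating rule that, applied as written, gives the results above. What stands is that no passage deliberately calls a transfer a re-admission; this follows from the wording.
- *The psychiatric gap depends on one reading.* Correct. A reader might infer that re-admissions in the psychiatric stratum are certainly under-counted. The document does not support that, because the eligibility usage of general would include psychiatric wards. But that usage opens the intensive care gap instead, so the conflict with the completeness claim remains.
- *The outcome is all-cause.* A reader might also infer that counting planned stays is an error. It is not. The Study Objective refers to re-admissions without limiting them to unplanned or drug-related ones. Removing planned stays would be a preference.
- *The ER half limits the damage.* The ER rule accepts any hospital emergency room, so some missed returns enter the composite that way. This stands, and it is a reason not to overstate the effect.

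**Conclusion.** The point holds as an inconsistency in a stated outcome definition that should be corrected. The rule cannot deliver the completeness that the same section claims, whichever way general is read. It also admits direct transfers, and possibly discharge-day services of the index stay, as events.

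The consequence is limited to the secondary outcome, including its comparison by unit type, and to its use in the loss-to-follow-up check and the board's quarterly rates. The primary outcome and the sample size are unaffected. The size is unknown, and the values in the illustration are assumptions.

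Two stronger conclusions might be drawn and should not be. One is that the measure fails to capture return to hospital for the enrolled patients: 26 of 28 units are medical or surgical, general-hospital stays outside the study centre are captured, and ER visits are counted separately. The other is that eligibility should require discharge to the community: that would narrow the population by an event after allocation, and it is unnecessary once transfers are handled in the outcome definition.

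**What to change.** In Outcome Assessment, replace the re-admission rule with a definition that has these parts:

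- a new inpatient stay in any acute, intensive care, psychiatric or specialised hospital unit;
- starting after the index discharge date and within 30 days of it;
- an inpatient service at another hospital that continues directly from the index stay is treated as part of that stay.

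Keep the outcome all-cause, with planned stays included, and leave the eligibility criteria unchanged. Use the same definition for the loss-to-follow-up check and the board's reports.

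The establishment, location and date of each service come with the claims, and the index discharge date is already abstracted from the chart, so no new data source is needed. The cost is a little more claims coding and a slightly changed event count.
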